## Abstract

**Background:**

Digital interventions for older adults may significantly extend preventive action to postpone disability and preserve health-related quality of life. However, more evidence is needed from multi-domain interventions using broad-scale objective and self-report assessments and intra-individual change data-analytical techniques.

**Method:**

SMART-AGE examines the effect of an app-based multilevel treatment designed to enhance social participation, physical fitness, and health awareness. The target population comprises healthy and community-dwelling adults 67 years and older with basic digital skills in two socially diverse communities. Treatment relies on an Android-based tablet computer, on which three apps offering interventions in the core areas of social participation, physical fitness, and health awareness are pre-installed. A feedback app designed to provide participants with a feedback option at any time is also offered. Participants are randomly assigned to three intervention arms and assessed at baseline and after 3 and 6 months. Arm 1 receives the full intervention, consisting of the social participation app, the physical fitness app, the health awareness app, and the feedback app. The health awareness app is available in months 4 to 6, meaning that participants receive the full three-app intervention only in the second half of the intervention period. Arm 2 receives the social participation app and the feedback app throughout the intervention. Arm 3 serves as an active control condition in that a stand-alone tablet with a low-dose introduction to publicly available standard apps is provided. The data protocol includes assessment of three primary outcome domains: social support and loneliness, motor capacity and physical performance, and health awareness and health locus of control. Potential moderators (e.g., cognitive function, depression) as well as various technology-oriented constructs (e.g., skills, acceptance) are also assessed. App use data are automatically collected across the full intervention interval in arms 1 and 2. Data management is conducted within a cloud-based REDCap architecture. Feedback recordings via the feedback app are collected in arms 1 and 2 and undergo qualitative analysis.

**Discussion:**

The SMART-AGE intervention aims to enhance core domains of health-related quality of life in community-dwelling older adults through an app-based multi-domain intervention and a user-centered approach.

**Trial registration:**

German-Clinical-Trials-Register, DRKS00034316. Registered 29-May-2024, https://drks.de/search/en/trial/DRKS00034316. The study’s design and hypotheses were also pre-registered in the Open Science Framework (OSF) prior to study enrollment (10.17605/OSF.IO/YQEBW, 2023–04-28).

**Supplementary Information:**

The online version contains supplementary material available at 10.1186/s13063-026-09641-3.

## Introduction

The randomized controlled trial “Smart Aging in Community Contexts: Testing Intelligent Assistive Systems for Self-regulation and Co-regulation under Real-Life Conditions” (SMART-AGE) aims to strengthen the evidence on app-based multi-domain interventions as a large-scale preventive tool for healthy older adults. This accords well with the broader digital transformations among older populations, which promise significant benefits but also involve potential challenges and risks [1–3].

## Background and rationale

SMART-AGE is designed as a complex intervention trial (see also [4]) that targets three intervention domains (social participation, physical fitness, health awareness) in various combinations. An increase in social participation is defined as enhanced social support, reduced feelings of loneliness, and an expansion of social networks. Improvements in physical fitness are reflected in increased muscle strength, better balance, and enhanced gait control. An increase in health awareness is understood as improved self-monitoring of health and stronger beliefs in one’s own ability to influence health through personal behavior (i.e., internal health locus of control). In addition, a direct effect of app use on technology skills and technology attitudes is expected.

SMART-AGE’s conceptual background for doing preventive app-based multi-domain interventions builds on the World Health Organization’s (WHO’s) well-established model of the International Classification of Functioning, Disability and Health (ICF) [5]. According to the ICF, preventive interventions should primarily support older adults in maintaining or regaining their ability to function. Functioning here means being able to use one’s physical and mental capacities in daily activities and social life, always in interaction with the surrounding environment. Digital technologies offer an increasingly important component of facilitating environments in the lives of older adults able to enhance and optimize functioning [6–8]. Building on the ICF as a framework for public health prevention, we assume that enhancing social participation, physical fitness, and health awareness via digital interventions constitutes an important strategy to support quality of life (QoL) in older age [9]. We combine in SMART-AGE the strengthening of these critical resources with a user-centered design approach in that we engage participants in systematic app-based feedback loops along the full intervention period (Fig. 1).

**Fig. 1 Fig1:**
[figure not shown]
Overview of the app-based multi-domain intervention package in SMART-AGE

### Digital strategies for enhancing social participation

Sustaining social participation and relations while mitigating loneliness in older adults is of paramount importance for QoL in later life [8, 10]. Social factors are integral to healthy life expectancy at large, as they are associated with a decreased risk of depression [11], dementia-related disorders [12], premature mortality [13], and enhanced well-being and satisfaction with life [14]. Furthermore, established theories of behavior change emphasize the pivotal role of social factors, including support and connectedness, in both initiating and sustaining behavioral changes as well as in promoting cognitive performance [15–17]. In the field of digital apps promoting social participation the “Personal Reminder Information and Social Management System” (PRISM), developed by Czaja et al. [6] stands out due to its breadth of social domains targeted as well as the rigor of evaluation. In a randomized controlled trial involving older adults aged 65 years and above, who lived alone with minimal prior computer and internet use, PRISM users demonstrated a significantly greater reduction in loneliness (*d* = 0.17) and a more pronounced increase in perceived social support (*d* = 0.28) compared to the control group after 6 months. Moreover, PRISM users exhibited a notable enhancement in computer proficiency (*d* = 1.11). SMART-AGE also builds in the area of social participation on additional previous research as work by Kawaguchi et al. [18] and Neal et al. [19]. In SMART-AGE, a PRISM version adjusted to German conditions, named smartVERNETZT, is deployed.

### Digital strategies for enhancing physical activity

Besides its most important role for social participation, enhanced physical fitness in later life comes with multi-level positive effects on various health domains (e.g., cardio-vascular, cognitive), maintenance of functional independence, as well as supporting fall prevention [20, 21]. Meanwhile, a range of reviews and meta-analyses showed that app-based mobile interventions are effective and highly promising for altering physical fitness and activity [22–24]. Additionally, digital apps contribute to improving accessibility, scalability, cost-effectiveness, and equity in healthcare [25]. A prime example is the app Keep On Keep Up (KOKU). Previous studies on KOKU demonstrated that users found the program appealing, motivating, and entertaining after 6 weeks of independent and unsupervised usage [26]. SMART-AGE also considers the evaluative studies conducted by Daniels et al. [27] and van Het Reve et al. [28]. In the SMART-AGE study, a German version of KOKU is used.

### Digital strategies for enhancing health awareness

Apparently, issues of health literacy, health awareness, and health self-monitoring are critical for health maintenance, prevention, and health-promoting behaviors. In agreement with WHO’s view on healthy aging [29], the process of enabling older individuals to take control over their health is key for SMART-AGE’s approach to health. It could be demonstrated that digital tools, especially digital self-monitoring systems, have the potential to support health literacy and awareness [7]. Initial evidence has shown that the use of these tools by older adults is feasible and goes along with a positive effect on health behavior and the management of (chronic) diseases and multimorbidity [30–32]. Primary outcomes for app-based interventions in this area include health locus of control, health knowledge, and motivation to monitor one’s health. The smartIMPULS app is implemented for these purposes in the SMART-AGE study.

### Digital strategies for enhancing feedback provision in a user-centered design with participatory design approach

By systematically focusing on the needs, priorities and critique of the target group, the likelihood that apps can be developed that promote high user acceptance and compliance is much increased [33–35]. In contrast to traditional methods such as focus groups and structured interviews, which are also integral to the user-centered design process, real-time feedback may better capture the challenges users face during actual usage [36, 37]. Doing so, a newly designed app (smartFEEDBACK) aims to bolster the user-centered design approach by real-time feedback generation across the full trial length. Details and functionalities of the apps used in SMART-AGE are provided below.

In conclusion, previous research has yielded encouraging findings on digital interventions, providing a solid foundation for SMART-AGE. However, most previous research took a single-domain approach, thereby overlooking the potential effects of combining different digital apps. For instance, while app-based interventions have been successfully evaluated previously in domains such as physical activity [e.g., [27, 28]] or social participation [e.g., [6, 18, 19]], little is known about the effects of their integration within a multi-domain framework.

## Objectives

According to our preregistration (see below), objectives of the SMART-AGE trial are as follows: Can the regular use of the offered apps (1) prevent or reduce loneliness and promote social support (particularly smartVERNETZT), (2) improve motor capacity (particularly KOKU), (3) increase health self-awareness and health-related control beliefs (particularly smartIMPULS), and (4) increase technology-related skills and the acceptance of technology?

To address these objectives, we decided for an intervention scheme as follows: a full intervention group (IG), a partial IG, and an active control group (CG). An active CG was installed to ensure that observed effects can be attributed to app use and not simply to the provision of a tablet to the participants coming with some social attention. In the full intervention condition, the participants will have access to all of the SMART-AGE specific apps, namely smartVERNETZT, KOKU, smartIMPULS, and smartFEEDBACK. In the partial intervention condition, the participants will have access to two SMART-AGE specific apps, namely smartVERNETZT (containing all standard apps) and smartFEEDBACK. This arm allows us to investigate the impact of the smartVERNETZT app without the co-use of other apps that also aim to improve the quality of life. It also serves as a most direct comparison to the previous PRISM trial [6]. Participants in the active CG will just be given the device and receive a basic introduction to publicly available and pre-installed standard apps (e.g., calendar app, e-mail app). In all of the three treatment arms, participants will receive a tablet and be given a short introduction on how to use a tablet in general.

Hypotheses based on these treatment variations are as follows:Participants who use a tablet equipped with the smartVERNETZT app (full and partial IG), which encourages social networking and participation, are expected to experience lower levels of loneliness and higher levels of social engagement compared to those using a tablet with only standard applications. This effect is expected to be even larger in the full IG than in the partial IG due to the synergistic benefits derived from using all apps designed to enhance quality of life.Participants who are in the full IG (who all have access to smartIMPULS) have increased health-related self-awareness and health-related control beliefs, compared to the active control and the partial IG, who both do not have access to smartIMPULS. Between the latter two groups, we do not expect any differences in health-related self-awareness and health-related control beliefs.Participants who are in the full IG (who all have access to KOKU) will show better gait performance and motor functioning, compared to the active control and the partial IG, who both do not have access to KOKU. Between the latter two groups, we do not expect any differences in gait performance and motor functioning.Over time, participants using a tablet will report greater technology acceptance and develop technology-related skills than before using a tablet. This increase in technology acceptance and technology-related skills is larger for participants in the full and partial IG. In addition, exploratory analysis will give more insight into the dose–response relationship between the amount of apps and their impact on technology acceptance and technology-related skills***.***

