### Intervention

SMART-AGE’s digital intervention builds to a large extent on previously successfully evaluated tools [6, 40]. In this context, smartVERNETZT represents the German adaptation and further development of the successfully tested PRISM system [6]. The app KOKU also underwent intensive testing within British public health improvement efforts [26, 40]. The app smartIMPULS represents the translation of an earlier system completely focusing on geriatric patients to healthy older adults (project: SINQ-Service integration and network management to improve social coexistence of geriatric patients in the community [41]). All apps underwent in SMART-AGE additional testing to assess their usability and feasibility. Focus group interviews with nine participants who used smartVERNETZT and smartFEEDBACK for at least 7 days indicated that the app was perceived as engaging and user-friendly [42]. Internal pilot testing of KOKU confirmed previous findings [26], suggesting that the app was perceived as easy to use, useful and enjoyable. Given the new development of smartIMPULS based on an earlier geriatric patient version, a 6-week pilot study with 30 participants was conducted, in which the system achieved a score of approximately 77 in the System Usability Scale [43], which indicates good usability [44]. Based on feedback in pre-studies, the user surface and content of the apps were further optimized.

The programming of the apps smartVERNETZT, smartIMPULS, and smartFEEDBACK was conducted by the Institute of Computer Science at the University of Heidelberg. The apps are accessed via a tablet (Lenovo M10 FHD Plus). Studies indicate that tablets are well-accepted by older individuals due to their intuitive gesture control and convenient size [45].

The usage of the apps is monitored, and in case of 2 weeks of non-use, a single reminder email is sent to the tablet. In addition to digital and analog user manuals and instructional videos, a helpline (via email and phone) has been established. For details on data privacy and security measures related to the apps, please refer to the section “Data storage, data processing, and data quality.” Images of the apps are provided in the supplement (see Appendix-A1). Table 1 provides an overview of the contents of apps used.

**Table 1 Tab1:** Overview of Contents of Apps Used in SMART-AGE

Name of app	App feature/content

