### Outcomes

There are four primary outcome domains in this study that will be compared across all three study arms:Health-related self-awareness, control beliefs, and self-efficacy, which includes measures like the Health Locus of Control Scale [48], Health Literacy [49], Adapted Health Consciousness Scale [50], and Self-efficacy [51];Motor capacity and performance, which includes measures like the Timed Up and Go Test [52] and movement sensor-based physical activity parameters (e.g., steps per day) using Axivity AX6 sensors;Loneliness and social support, which includes measures like the UCLA Loneliness Scale [53], Lubben Social Network Scale [54].Technology acceptance, competence, and usage, which includes measures like Computer Anxiety [55] and End User Frustration [56].

Another important part of the assessment architecture in SMART-AGE is the generation of multiple usage data while the apps are used by study partners. This includes, for instance, the assessment of weekly usage frequency and intensity (e.g., total time spent using the apps, number of interactions within the apps), as well as the analysis of app-specific features used—such as whether video calling was utilized in smartVERNETZT, how many training levels were completed in KOKU, or how many questions were answered in smartIMPULS or smartFEEDBACK. These metrics will be analyzed over time and across multiple apps to identify usage patterns and dynamics, which can then be related to changes in the targeted outcomes.

A complete list of all assessments, encompassing all measures related to the main and secondary hypotheses, as well as demographic measures that describe the sample is provided in Appendix Part 2. In addition, we also collect objective user data from the SMART-AGE apps to evaluate in more detail the app usage.

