### Sample size

The sample size was determined through an a-priori power analysis to ensure adequate power for the planned structural equation modeling analyses. We will study the effect of the intervention groups as contrasted with the active control condition on main outcomes using latent change models, in which each of the four main outcome domains will be represented in latent space by at least three manifest variables. Assuming measurement invariance across the three study time points, the two intervention sites, and the two experimental groups and one active control group, this results in a model with 128 estimated parameters and 16,162 degrees of freedom. With the requirement of five participants per estimated parameter, an expected dropout rate of 10% and a further increase to balance the strata, we plan to collect a sample of 720 participants to be analyzed based on an intention-to-treat analysis, that is, all participants having entered the study at baseline will become part of the statistical effect analysis independent of their “fate” along the full observational period. Moreover, at each of the three study time points for each of the three groups, the planned sample size meets Browne and Cudeck’s [57] recommendations for model testing based on the close fit hypothesis (H0, ε ≤ 0.05; H1, ε ≥ 0.08; *α* = 0.05) using the root mean square error of approximation (RMSEA; 44). This provides a statistical power of 1 – *β* > 0.99 for the main model across all study time points as well as for analyses conducted at a single time point, ensuring that the study has sufficient power to reject the model if its fit to the empirical data is inadequate.

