### Statistical methods

Our main hypotheses will be tested using multilevel and structural equation models, following an intention-to-treat analysis. We will test the effect of experimental group on primary outcomes separately for each outcome with a 3 × 3 factorial design multilevel model with the between-subjects factor *study arm* (active CG vs. partial IG vs. full IG) and the within-subjects factors *study time point* (study start vs. 3 months vs. 6 months), followed by post-hoc comparisons controlling for the family-wise error rate. Models will include random intercepts for each participant and their place of residence. As covariates, we will consider participants’ gender, their age, and their frequency and intensity of app usage. We plan to report all analyses with and without the inclusion of these covariates. Where the assessment of primary outcomes is only possible during HVs, we will remove the 3-months level from the within-subjects factor *study time point*.

In addition, we will test the effect of experimental groups on primary outcomes first separately for each outcome and then jointly for all four primary outcomes using latent change models. In these models, the multilevel structure of the data will be accounted for by multigroup comparisons to examine whether (a) the effects of the two IGs are larger than the effects of the active CG (see hypotheses), whether (b) the effects of the full IG are larger than the effects of the partial IG (see hypotheses), and (c) by which individual and/or sociodemographic variables the effects of the two interventions on the four primary outcome variables are moderated.

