## Discussion

Robust evidence on the use of digital technology as a prevention means to strengthen multiple resources important to maintain QoL in old age is lacking. In terms of strengths, SMART-AGE first aims to improve this situation based on a complex trial design and a multimodal intervention by means of four interconnected apps. Target areas include enhancing social participation, increasing physical activity, and boosting health awareness, as well as the intensive collection of feedback, while using the respective apps.

Second, the exploitation of expected data including user-centered feedback and objective usage information may hold the potential for important insights. For example, effects observed at the primary outcome level (loneliness and social support, motor capacity and performance, health-related self-awareness and health control beliefs, technology acceptance and competence) can be linked with the objective app usage patterns and user feedback. This enables a deeper understanding of why and how the interventions work or do not work, and for whom.

Third, SMART-AGE also follows a multilevel approach of self-report data, performance-based data, and tracking data for assessing primary outcome domains. Therefore, possible differential effects of interventions on subjective versus objective assessment levels can be tested.

Fourth, SMART-AGE allows for examining short-term (3 months) and medium/long-term (6 months) effects of app use. Given the short cycles of technology and product innovation, we posit that 6 months is a sufficient time period for robust effect testing. For example, SMART-AGE’s digital appliances do not use speech control features, but it can be expected that speech control and speech assistance will much expand also in the area of digital preventive tools, e.g. [64].

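### The objectives ask what regular use of the apps does, but the intention-to-treat contrast estimates the effect of being given them, and the planned usage analyses cannot close that gap

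*Protocol article*

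**What the plan says.** The protocol article, Objectives, puts four aims under one causal question about use: "Can the regular use of the offered apps (1) prevent or reduce loneliness and promote social support (particularly smartVERNETZT"), followed by motor capacity, health awareness and control beliefs, and technology skills and acceptance. Regular use is not defined. The same section says "An active CG was installed to ensure that observed effects can be attributed to app use". The hypotheses that follow are contrasts between arms. The motor one, for example, is worded by access: "Participants who are in the full IG (who all have access to KOKU) will show better gait performance and motor functioning".

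Statistical methods states: "Our main hypotheses will be tested using multilevel and structural equation models, following an intention-to-treat analysis". Sample size adds that "all participants having entered the study at baseline will become part of the statistical effect analysis", whatever happens to them later.

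Use comes in elsewhere:
- Outcomes says usage metrics will be analysed for patterns, "which can then be related to changes in the targeted outcomes".
- The Discussion says of linking outcome effects with usage patterns and user feedback: "This enables a deeper understanding of why and how the interventions work or do not work, and for whom".
- Statistical methods lists frequency and intensity of app usage among the covariates for the main models. Results are to be reported with and without covariates, and neither version is named as primary.
- Statistical methods also leaves exclusion criteria based on app usage to an outcome-blind analyst after data collection, because prior knowledge of usage is lacking.

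Use is voluntary: "in case of 2 weeks of non-use, a single reminder email is sent to the tablet". According to the Abstract, app use data are collected in arms 1 and 2.

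**The concern.** The question asked and the quantity estimated are different. Intention to treat averages over those who use the apps and those who do not. That is a sound and useful quantity, but it is the effect of use only if nearly everyone uses the apps regularly, and the article does not assume this. A null arm contrast would leave open whether the apps do not work or were not used.

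The analyses that look at use lack the protection of randomisation. Motivation, health and digital skill can drive both use and change, and people who improve may keep using the apps. An association between use and change can therefore arise with no app effect at all, yet the Discussion presents it as informative about mechanism.

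**Working it through.** **1. What the plan's own figure contains.** Sample size: 128 parameters × 5 participants = 640. Allowing for 10% dropout, 640 / 0.90 = 711.1, so 712. The next multiple of 72 (Recruitment) is 720, or 240 per arm. The figure reproduces. It contains no treatment effect and no usage rate, so the article offers nothing from which to size dilution.

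**2. Question against analysis.**
- Objectives: effect of regular use.
- Hypotheses: differences between arms, with the health and motor ones defined by access.
- Main analysis: everyone entered, by allocation. This matches the hypotheses but not the wording of the objectives.
- Usage linked to change: a comparison among self-selected users.

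**3. How the two quantities relate.** Let p be the share of regular users in an intervention arm. Arm 3 does not have the study apps. If assignment acts only through regular use and lighter use brings no benefit:

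arm contrast = p × effect in regular users, so effect in regular users = arm contrast / p.

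The article gives no p. For an assumed p of 0.9 to 0.5 the multiplier is 1/0.9 = 1.11 to 1/0.5 = 2.0. As an illustration, take the two differences that the article cites from the earlier PRISM trial as arm contrasts:
- 0.17/0.9 = 0.19 to 0.17/0.5 = 0.34
- 0.28/0.9 = 0.31 to 0.28/0.5 = 0.56

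**4. Self-selection with no app effect.** If an unmeasured trait correlates a with use and b with change, and the apps do nothing, use and change still correlate at a × b. Arms 1 and 2 with 10% dropout give 480 × 0.90 = 432 people. Power is by Fisher z, two-sided 0.05.
- a = b = 0.1 to 0.2: correlation 0.01 to 0.04, significant in about 5% to 13% of trials.
- a = b = 0.3 to 0.4: correlation 0.09 to 0.16, significant in about 46% to 92%.

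All values of a and b are assumptions. The range shows that a false association is possible; it does not say how likely one is.

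**5. Usage as a covariate.** Use is measured after randomisation and is itself affected by arm. Arm 3 has no study-app use. The Participant timeline switches on monitoring at the first visit before randomisation, so some tablet use may be recorded in arm 3, but not use of apps that it lacks. If use in arm 3 is set to zero, the adjusted arm coefficient compares control with intervention participants extrapolated to zero use, which removes any effect that runs through use. If it is left missing, the control contrast rests on a model for a quantity that does not exist there. Either way the adjusted contrast is neither the effect of allocation nor the effect of use.

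**The case against.** The strongest reply is that the hypotheses, not the introductory question, are what the trial tests, and these are arm contrasts that intention to treat tests directly. That stands. A reader might infer that the trial leaves its own question unanswered; the article does not support this. What is missing is the effect under regular use. The sentence on the active control, read in full, mainly separates the apps from the provision of a tablet and some social attention.

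A reader might also dilute the cited d = 0.28 by an assumed 50% to 90% use. This gives 0.14 to 0.25, and power at 240 per arm falls from 87% to 34%–79%. The arithmetic is right but the premise is not supported. The article describes 0.28 as a difference from control in a randomised trial, so non-use may already be in it. The comparison is also an unadjusted two-arm one, whereas the plan uses repeated-measures and latent change models, and the social hypothesis sets both intervention arms against control. These power figures, and the false-association rates above, are illustrations only.

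The usage links in Outcomes and the Discussion are worded cautiously in places and are not declared confirmatory tests. That is fair, but usage as a covariate sits in the main models, and the claim about why and how is explicit. Finally, a complier analysis could be in an analysis plan that is not shown. Its absence alone is no finding; the finding is the mismatch in what is stated.

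**Conclusion.** The point holds in a limited form. The objectives are worded as effects of regular use, the main analysis estimates the effect of being given the apps, and the stated routes to use condition on self-chosen post-randomisation behaviour. The randomised contrasts remain valid tests of the hypotheses if they are run without usage covariates and without usage-based exclusions. The article does not fix this: neither the model with covariates nor the one without is primary, and usage-based exclusions would conflict with analysing everyone who entered.

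The size of the dilution and of the self-selection bias is unknown. The multiplier of 1.1 to 2.0 rests on an assumed share of regular users, no benefit from lighter use, and no effect of assignment other than through use.

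**What to change.** 1. Word the objectives as the effect of being given the apps.
2. Name the intention-to-treat model without usage covariates or usage-based exclusions as primary.
3. Label usage-change associations and usage-adjusted models as exploratory and non-causal, in Outcomes, Statistical methods and the Discussion.
4. For the regular-use question, add a supplementary complier-average causal effect analysis with randomised arm as instrument, mainly arm 2 against arm 3. Both arms receive the second home visit and only arm 2 receives smartVERNETZT. The estimate is for the arm 2 package, which includes smartFEEDBACK and more app instruction. Let the outcome-blind analyst set the threshold for regular use, and add a sensitivity analysis at any use, which relaxes the assumption that lighter use brings no benefit.
5. Report an arm 1 against arm 3 version only for the whole package. It cannot isolate KOKU or smartIMPULS, and the Discussion concedes that home visits differ by arm, so assignment may act other than through use.

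The cost is wording plus one supplementary analysis on data already logged. The complier interval is wider by about 1/p, that is 1.1 to 2.0 times for the assumed 90% to 50% use, before allowing for uncertainty in p. The assumption that assignment acts only through use cannot be tested.
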